## 6.2 Randomisation, blinding and treatment allocation

Patients are included after signing the Informed Consent form. Patients will be stratified per clinic. Randomisation is done by web based computer application. Each centre will have its own username and password with a specific randomisation in blocks with a variable amount of patients. Block randomisation is used to get an equal distribution of patients in each treatment group for the interim and final analysis. Per randomisation patients characteristics like gender and date of birth are asked to prevent scrambling.

Each centre should randomise at least 50 patients to receive an equal distribution over the participating centres. Patient and assessors are blinded for the intervention by the patient. After 3 months follow-up, the treatment arm is communicated with the patient.

All patients are followed according to the intention-to-treat principle. Patients will be registered using a patient number, date of birth and study number and all other data will be coded by linkage to the study number.

An analysis plan will be enclosed as an addendum of this protocol 4.1 and before the study will be de-blinded.

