# SUMMARY

**Rationale:** Fibrin Sealant is known to have some potential benefits for intraoperative use, especially in the acceleration of the coagulation cascade. Most studies with fibrin glue are focussing on the reduction of allogeneic blood transfusion and the possibilities to reduce costs. Firstly, fibrin sealant was made from patients’ blood plasma but the logistic problems made introduction in general hard. Now Sanquin has produced a CryoSeal (fibrin sealant) made of single-donor plasma which can be used during surgery. This application is already used in cardiothoracic surgery.

**Objective:** Is the application of CryoSeal (CS) in primary total knee replacement surgery beneficial for the patient with respect to a faster track and improved postoperative rehabilitation. The beneficial effect may be due to quicker functional knee rehabilitation, by pain reduction, better mobilisation and improved quality of life during the early postoperative period.

**Study design:** Multicenter, randomised controlled trial stratified by clinic.

**Study population:** Patients aged above 18 years scheduled for primary total knee replacement (TKA) because of osteoarthritis or rheumatic arthritis, meeting all the inclusion criteria and none of the exclusion criteria, are eligible for inclusion in the study.

**Intervention:** The intervention is the application of CryoSeal during surgery according to the standardised manner. The control group will receive standard care.

**Main study parameters/endpoints:** Primary endpoint: Difference in extension knee function 2 and 6 weeks after surgery. Secondary endpoints: postoperative complications, Pain score, knee function Flexion/Extension, Barthel score (day 3); Outpatient department scores (2 weeks, 6 weeks and 3 months, 1 year): Complications, Pain knee function, KSS, KOOS, SF-12, IPQ-K and EQ5D. A pre- and postoperative hand strength measurement will be performed since this might be a predictor of outcome after TKA. (Taekema 2010). Where possible, an actual physical activity measurement will take place to objectively analyse pre- and post operative acitivity level. (Groot, de 2008)

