# 3. STUDY DESIGN

The study is a randomised, multi centre trial in orthopaedic surgery in patients who receive a primary total knee replacement. Patients will be randomised in two groups. The intervention group will be treated with CryoSeal per operative and the control group will receive standard care (no additional treatment during surgery). Patients will be stratified prior to randomisation in six strata occording to the the clinical site where the use of postoperative wound drain is the standard procedure. No consensus between the sites exists on the usage of the latter.

Patients and observers will be blinded for treatment until 3 months postoperative.

See Flow chart next page

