**Outpatient department (2 weeks, 6 weeks and 1 year)**

- Complications (all timepoints)
- Pain score (all timepoints)
- Knee function F/E (all timepoints)
- KSS (6 wks, 1 year)
- Oxford Knee Score (OKS) (2, 6 wks, 1 year)
- Barthel index (2, 6 wks and 1 year)
- KOOS (6 wks and 1 year)
- SF-12 (6 wks and 1 year)
- IPQ-K (6 wks and 1 year)
- EQ5D (2, 6 wks and 1 year)

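### Patients learn their arm at 3 months, with no stated reason, so the 1-year self-reported secondary outcomes are collected unblinded; the primary endpoint and all 2- and 6-week outcomes are not affected

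*Combined protocol and SAP*

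**What the plan says.** Two places in the protocol set the length of blinding. Section 3 (Study design) says: "Patients and observers will be blinded for treatment until 3 months postoperative". Section 6.2 says that patient and assessors are blinded, and then: "After 3 months follow-up, the treatment arm is communicated with the patient". Section 6.2 mentions disclosure to the patient only.

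The flow chart in section 3 gives the outpatient visits as "Outpatient department (2 weeks, 6 weeks and 1 year". At 1 year it includes pain ("Pain score (all timepoints"), the Oxford score ("Oxford Knee Score (OKS) (2, 6 wks, 1 year"), "KOOS (6 wks and 1 year", "SF-12 (6 wks and 1 year", and also Barthel, IPQ-K, EQ5D, KSS, knee flexion and extension, and complications.

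The Summary counts late outpatient scores among the secondary endpoints, but with a different visit list: "Outpatient department scores (2 weeks, 6 weeks and 3 months, 1 year". It names pain, knee function, KSS, KOOS, SF-12, IPQ-K and EQ5D at those visits, but not the Oxford score or Barthel. Section 6 brings in the function scores as secondary endpoints by reference to the flow chart. Table 1 in section 6.3 has no 3-month column.

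The analysis plan addendum of 15 May 2013 lists outcomes at 6 weeks and at 1 year. It has the database closed and de-blinded more than six weeks after the last operation.

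**The concern.** The trial blinds patients and assessors for the early assessments and then plans to tell patients their arm well before the last one. The comparator is standard care with nothing added during surgery, so disclosure tells control patients that they did not receive the product. Some nine months later the same patients rate pain, function, quality of life and illness perception. These are outcomes that a patient's beliefs about treatment can influence, and IPQ-K measures perception directly.

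What is at stake is how the 1-year secondary results are read. If the arms differ at 1 year, or if the difference changes between 6 weeks and 1 year, the plan offers no way to separate an effect of the sealant from an effect of knowing the arm. Nothing in the visible documents depends on patients knowing at 3 months, so the weakness looks avoidable.

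**Working it through.** **Timing.** The inputs are disclosure after 3 months (sections 3 and 6.2) and outpatient visits at 2 weeks, 6 weeks and 1 year (flow chart). Taking 3 months as about week 13 and 1 year as about week 52:

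- 2- and 6-week visits: before week 13, so blinded.
- 1-year visit: 52 − 13 = 39 weeks after disclosure, so the patient knows the arm.

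**Which outcomes fall on which side.**

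| Outcome | Time points | Blinding status under the plan |
|---|---|---|
| Primary: change in knee extension | 2 and 6 weeks | Blinded |
| Pain, Oxford, Barthel, EQ5D | 2 and 6 weeks | Blinded |
| KOOS, SF-12, IPQ-K | 6 weeks | Blinded |
| Pain, Oxford, Barthel, KOOS, SF-12, IPQ-K, EQ5D | 1 year | Patient knows the arm |
| KSS, goniometry | 1 year | Unclear: section 3 ends observer blinding; section 6.2 mentions telling only the patient |

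**The 3-month assessment.** The Summary lists one. The flow chart and Table 1 do not. If it takes place, the plan does not say whether it comes before or after disclosure.

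**Size.** The plan states no figure for this bias, so there is nothing to reproduce and a range must be assumed. Suppose there is no true effect and knowledge of the arm shifts the mean difference by b (in SD units). With n analysed per arm and a two-sided 5% test:

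- SE = √(2/n). With n = 250 (section 4.4, taking all patients as analysed at 1 year), SE = √0.008 = 0.089 SD.
- Shift of the test statistic: z = b/SE.
- Rejection rate = Φ(z − 1.96) + Φ(−z − 1.96).

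| Assumed b (SD) | z | False-positive rate per endpoint |
|---|---|---|
| 0 | 0 | 5% |
| 0.10 | 1.12 | 20% |
| 0.15 | 1.68 | 39% |
| 0.20 | 2.24 | 61% |

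Section 4.4 allows 400 to 600 patients in total. With 200 per arm, SE = 0.100, and shifts of 0.1 and 0.2 SD give z = 1.00 and 2.00, hence about 17% and 52%. With 300 per arm, SE = 0.082, giving z = 1.22 and 2.45, hence about 23% and 69%. More patients do not dilute the problem: a fixed bias is detected more often as n grows.

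**The case against.** The strongest defence is that the trial answers its question inside the blinded period. Section 2 defines benefit as early rehabilitation at 2 and 6 weeks, and section 6 stresses the short term. Open late follow-up after a blinded early phase is a recognised design. This stands, and it limits the point to late secondary outcomes. A reader might infer that the main result is compromised; the documents do not support that.

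A reader might also infer that the disclosure serves no purpose. The documents only show that no reason is stated. The consent pages were removed before review, and a commitment to patients could be set out there.

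It is tempting to say that 1-year assessors are unblinded as well. Section 3 points that way, but section 6.2 speaks only of telling the patient. The documents leave it open.

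The false-positive rates rest wholly on an assumed shift. Nothing in the documents fixes its size, its direction, or whether it lasts nine months, and full follow-up is assumed. Section 8 specifies no 1-year comparison between arms. The addendum's 1-year outcome list follows observational questions, many of them not about the randomised comparison, for which knowledge of the arm matters less. These points weaken the figures as a description of this trial. They do not remove the exposure, because the Summary makes the 1-year scores secondary endpoints and the addendum plans analyses of the secondary endpoints by arm.

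Finally, the change comes late. The addendum already gives a realised count of 73 patients for one drain type at one site, so recruitment was advanced and some patients may have been told. A new rule would leave a 1-year cohort that is part blinded and part unblinded, split by enrolment date. That stands, and is why the fix needs a second part.

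**Conclusion.** The point holds for the 1-year self-reported secondary outcomes. Following the plan exactly means collecting them from patients who have known their arm for about 39 weeks, with no stated reason and no label to warn the reader. For 1-year KSS and goniometry the exposure is possible but not established. The primary endpoint and every 2- and 6-week outcome are untouched by this disclosure.

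The size of the bias is unknown. The 20% to 61% range holds only under an assumed shift of 0.1 to 0.2 SD with 250 per arm analysed and no true effect. It shows that a modest bias would matter at this sample size and is not an estimate for this trial.

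It would go too far to conclude that the 1-year results are worthless or cannot be set beside the early ones. Both can be reported, provided the 1-year self-reports are shown as unblinded. This is a change that should be made, not a threat to the trial's main conclusion.

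**What to change.** 1. In sections 3 and 6.2, keep patients and assessors blinded until the 1-year assessment is complete, and tell patients their arm only after that visit. Use the same wording on assessors in both sections.
2. State in the addendum that de-blinding the database for the early analysis does not release individual allocations to patients or 1-year assessors. As written, it can happen before late-enrolled patients reach 1 year.
3. For patients already told, record the disclosure date and report their 1-year outcomes as unblinded and supportive. If the rule has changed midway, show 1-year results separately for patients told before and after the visit.
4. If the sponsor has a reason for disclosure at 3 months, state it, and label all 1-year self-reported outcomes as unblinded and supportive.
5. Reconcile the Summary's 3-month assessment with the flow chart and Table 1. If the visit exists, state that it precedes disclosure.

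The cost is that patients wait about nine months longer to learn their arm, the amendment must be notified to the METC (section 10.2), and the consent wording must match. No extra patients or visits are needed. Items 3 and 5 remain useful even if enrolment is nearly complete.

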**6.3 Study procedures**

| **Evaluation** | **Pre-op** | **OR (day 0)** | **Postoperative** | | | | | | |
| --- | --- | --- | --- | --- | --- | --- | --- | --- | --- |
| **Day 1** | **Day 2** | **Day 3** | **Discharge** | **2 wks** | **6 wks** | **1 year** |
| **Medical History** |  |  |  |  |  |  |  |  |  |
| **Operation details** |  |  |  |  |  |  |  |  |  |
| **Clinical data** |  |  |  |  |  |  |  |  |  |
| **Laboratory assessment** |  |  |  |  |  |  |  |  |  |
| **Complications** |  |  |  |  |  |  |  |  |  |
| **Pain score** |  |  |  |  |  |  |  |  |  |
| **Function (F/E)** |  |  |  |  |  |  |  |  |  |
| **Barthel score** |  |  |  |  |  |  |  |  |  |
| **KSS** |  |  |  |  |  |  |  |  |  |
| **KOOS** |  |  |  |  |  |  |  |  |  |
| **SF-12** |  |  |  |  |  |  |  |  |  |
| **Oxford Knee Score** |  |  |  |  |  |  |  |  |  |
| **IPQ-K** |  |  |  |  |  |  |  |  |  |
| **EQ5D** |  |  |  |  |  |  |  |  |  |

Table 1; parameters and time points of measuring

## 6.4 Withdrawal of individual subjects

Withdrawal is not to be expected, as standard implants are being used and follow-up is not different from routine follow-up of knee prosthesis in general. Subjects can leave the study at any time for any reason if they wish to do so without any consequences.

## 6.5 Replacement of individual subjects after withdrawal

Withdrawal is not to be expected, as standard implants are being used and follow-up is not different from routine follow-up of knee prosthesis in general. If patients withdraw from the study they will not be replaced.

Patients that are already randomised but operation is rescheduled because of any reason, subjects will stay in the study without changing randomisation.

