## 4.4 Sample size calculation

We performed a sample size calculation for our primary outcome which is pre- to postoperative difference in knee extension angle at two weeks after surgery. We expect to find a difference between study arms of 10 degrees, which we also feel is clinically relevant. We have little prior data to base our calculations on, but we expect a standard deviation of 35 degrees in our primary outcome. We conclude that we need 250 patients in each arm to be able to detect the stated difference at significance level 4.9% with 90% power.

We have made a slight adjustment to the usual significance level of 5% because we plan to perform an interim analysis when a total of 250 patients have been included. At this time we will decide if the trial should be terminated early for efficacy or futility. If the trial continues, we will use the available data to estimate the standard deviation of the primary outcome. Based on this estimate, we will re-compute the sample size that is needed to achieve 90% power to detect a 10 degree difference between the study arms at level 5%. We will adjust the sample size accordingly. However, we will not include less than 400 patients or more than 600 patients.

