# 6. METHODS

## Study parameters and endpoints

Hypothesis

The hypothesis is that the application of CryoSeal (CS) during total knee replacement surgery is beneficial for the patient with respect to a faster track and improved postoperative rehabilitation. The beneficial effect may be due to quicker rehabilitation, by pain reduction, better mobilisation and quality of life (especially short time).

Primary endpoints

- postoperative knee function in extension difference as compared with preoperative extension function with goniometric at 2 and 6 weeks (in relation to secondary endpoints)

Secondary endpoints

- Grade flexion and extension difference after surgery
- Drain use or not
- Postoperative Hb/Ht
- Number of transfusions after surgery (according to appendix 1)
- Pain score
- Complications
- Total hospital stay and duration of rehabilitation
- Illness perception IPQ-K score
- Function improvement score (KSS, Barthel Index score, KOOS etc. see flowchart)
- Hand grip strength (measured with (Jamar) hand dynamometer)
- Activity Monitor

Study parameters

- Demographic data; gender, birth date (age), weight, length (BMI)
- Medical History; underlying diseases and home medication (including use of antibiotics prophylaxis and NSAIDs)
- Laboratory analysis; haemoglobin, haematocrit and blood view, CRP and erythrocyte sedimentation rate
- Operation details; anaesthesia, start- and end time of surgery, surgeon, type and time point placing and opening of drain, use of heparin, information about application of CryoSeal (if applicable), knee function after implantation of the implants
- Clinical data; number of transfusions (red cells, platelets and plasma), complications, removing drain, amount collected in drain, medication (including use of antibiotics and NSAIDs), discharge date
- Pain (score) at 24h post operative, and at 8:00 h each day until discharge from hospital.
- Rehabilitation; knee function during the first postoperative days, Barthel Index score and standard knee function scores (see Table 1).

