# 8. STATISTICAL ANALYSIS

Data will be analysed by the intention-to-treat principle. Demographic characteristics, variables from laboratory analysis and quantitative variables obtained from the clinical evaluation (Pain score, opioids consumption) will be reported as means, medians or percentages together with their standard deviations, as appropriate.

We will perform the following analysis of the primary endpoint. In all patients we test for a difference in mean pre- and post-operative extension angles between those with and without Cryoseal. Adjusting for pre-operative extension angles by analysis of covariance, we perform a two-sided test at level 0.049. In a secondary analysis, Fisher’s exact test will be used to determine the effect of use of fibrin sealant on adverse events. We will investigate whether the Cryoseal effect is modified by the use of a drain by adding drain use and the interaction between drain use and Cryoseal to the above analysis of covariance model. Also, effects within various other patients groups will be studied (e.g. gender, age, adipositas and rheumatic disorders)

Interim analysis and stopping rule:

We plan to perform a single interim analysis when a total of 250 patients have been included. At this time we will decide if the trial should be terminated early for efficacy. In all patients we test for a difference in mean pre- and post-operative extension angles between those with and without Cryoseal. Adjusting for pre-operative extension angles, we perform a two-sided test at level 0.005. If we are able to reject the null hypothesis, we terminate the trial and conclude efficacy of the treatment.

If the stopping rule is not met and the trial continues, we must set the level of significance of the final analysis to 0.049 to account for the fact that we performed an interim analysis. This is referred to as the O'Brien-Fleming rule.

Also, if the trial continues, we will use the available data to estimate the standard deviation of the primary outcome. Based on this estimate, we will re-compute the sample size that is needed to achieve 90% power to detect a 10 degree difference between the study arms at level 5%. We will adjust the sample size accordingly. However, we will not include less than 400 patients or more than 600 patients.

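### Section 4.4 claims 90% power at 250 per arm with no allowance for missing extension angles, and no rule covers a missing 2- or 6-week angle

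*Combined protocol and SAP*

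**What the plan says.** Section 4.4 defines the primary outcome for sizing as the "pre- to postoperative difference in knee extension angle at two weeks after surgery". It gives the inputs as "We expect to find a difference between study arms of 10 degrees" and "we expect a standard deviation of 35 degrees in our primary outcome", and concludes that "we need 250 patients in each arm to be able to detect the stated difference" at the 4.9% level with 90% power. No loss rate or inflation factor appears.

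Section 6.4 states "Withdrawal is not to be expected", on the ground that the implants are standard and follow-up is the same as in routine care. It also lets subjects leave at any time. Section 6.5 adds "If patients withdraw from the study they will not be replaced".

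Sections 4.4 and 8 plan a re-estimation after the interim analysis at 250 patients. Its only data input is the estimated standard deviation, and the total is held between 400 and 600.

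Section 6, under study parameters and endpoints, measures the primary endpoint "with goniometric at 2 and 6 weeks". Section 8 says "Data will be analysed by the intention-to-treat principle" and specifies an ANCOVA adjusted for the pre-operative angle. The addendum adds an according-to-treatment analysis. Neither section 8 nor the addendum says what is done when a 2- or 6-week angle is missing.

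**The concern.** There are two linked gaps.

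The first is in the stated power. The 250 per arm is the number to be enrolled, but the formula needs that many measured angles. Expecting no formal withdrawal does not cover a missed visit or an unrecorded goniometer reading in a multicentre trial. The re-estimation does not correct this, because it aims for 90% power as if every enrolled patient were measured.

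The second is in the analysis. An ANCOVA on the angle at one visit can use only patients with a reading at that visit, unless a rule says otherwise. A patient seen at 6 weeks but not at 2 would drop out of a 2-week analysis although a primary-endpoint measurement exists. That wastes data. If attendance depends on how well the knee is recovering, it can also bias the comparison, which a larger sample would not cure.

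**Working it through.** **Inputs.** Difference 10 degrees, SD 35, 90% power and 250 per arm come from section 4.4; two-sided level 0.049 from section 8; equal arms from section 6.2. The documents give no loss rate, so 5% to 20% is an assumed range.

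**The plan's own figure.** Number per arm = 2 × [35 × (z(0.9755) + z(0.90)) / 10]² = 2 × [35 × (1.969 + 1.282) / 10]² = 258.8, so 259. At level 0.05 it is 258. Neither gives 250. Power with n measured per arm is Φ(10 / (35 × √(2/n)) − 1.969). At n = 250 this is Φ(3.194 − 1.969) = 89.0%, so the stated 90% is reproduced to within about a point, with complete data.

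**Adding loss.** A missing fraction d leaves n × (1 − d) measured per arm.

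| Missing (assumed) | Measured per arm, from 250 | Power, from 250 | Power, from 259 | Power, from 300 (the cap) |
|---|---|---|---|---|
| 0% | 250 | 89.0% | 90.0% | 93.7% |
| 5% | 237.5 | 87.4% | 88.5% | 92.5% |
| 10% | 225 | 85.6% | 86.8% | 91.2% |
| 15% | 212.5 | 83.6% | 84.8% | 89.6% |
| 20% | 200 | 81.3% | 82.6% | 87.7% |

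The first point of shortfall comes from using 250 instead of 259, not from loss. The part due to loss is 89.0 − 87.4 = 1.6 points at 5% and 89.0 − 85.6 = 3.4 points at 10%.

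**Re-estimation.** If the interim SD is again 35, the rule as written (level 5%) returns 258 per arm, or 516 in total, with nothing added for loss. Inflating the 259 needed at level 0.049 by 1/(1 − d) gives 273 per arm (546 in total) at 5%, 288 (576) at 10% and 305 (610) at 15%. The 600 cap therefore covers at most 1 − 259/300 = 13.7% loss at SD 35.

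**Baseline adjustment.** Section 4.4 attaches the SD of 35 to the pre-to-post difference. If pre- and post-operative variances are equal (assumption) with correlation r, the ANCOVA residual SD is 35 × √((1 + r)/2). The loss that 250 per arm can absorb at 90% power is then:
- r = 0.5: residual SD 30.31, 195 needed, 1 − 195/250 = 22%
- r = 0.7: residual SD 32.27, 220 needed, 12%
- r = 0.9: residual SD 34.11, 246 needed, 1.6%
- r = 0.95: residual SD 34.56, 253 needed, so 90% is missed even with complete data

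The documents do not give r.

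**The case against.** The strongest reply is that the trial may well reach 90% power despite some loss. The planned ANCOVA is more efficient than the unadjusted calculation behind 250 per arm, and at a moderate correlation it would absorb 12% to 22% loss. The total can also rise to 600, where power at SD 35 is still 91.2% with 10% missing. Follow-up is routine care, which is a fair reason to expect few losses. All of this stands. A reader might infer that any loss makes 90% power unattainable, or that enrolment is fixed at 500. The documents support neither: r is not stated, and the sample size is adaptive.

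A reader might also infer that the plan prescribes a complete-case analysis. It does not. It promises intention-to-treat and is silent on missing angles, so complete-case is only the default outcome of an ANCOVA with no rule.

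Not replacing withdrawn patients is not itself an error, since it is consistent with intention-to-treat. Nor does keeping patients whose surgery is rescheduled create missing readings, because visits are timed from surgery.

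The reply leaves two things unanswered. Section 4.4 credits neither baseline adjustment nor the re-estimation against loss, so its 90% does not rest on them. And extra power from either source does not settle which patients enter the primary analysis.

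**Conclusion.** The concern holds in a limited form. On the protocol's own unadjusted calculation, the stated 90% is 89.0% with complete data, 87.4% with 5% missing and 85.6% with 10%. These figures assume SD 35, 250 enrolled per arm and loss rates that the documents do not supply. Baseline adjustment or a re-estimated total of up to 600 may recover some or all of the shortfall, so it is not established that the trial is underpowered.

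The power effect is moderate. The weightier gap is that no rule covers a missing 2- or 6-week angle, although measurements already scheduled at the other visit could be used. This does not invalidate the trial, but it leaves the primary analysis underspecified at a point that is cheap to settle in advance.

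**What to change.** 1. In section 4.4, restate the power at 0%, 5% and 10% missing 2-week angles. State an expected loss rate and use it in the re-estimation, dividing the required number by (1 − d), within the existing 600 cap. If recruitment has already ended, only the restatement applies.

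2. In section 8 and the addendum, analyse extension with one longitudinal model: baseline extension, clinic, arm, visit (2 and 6 weeks), arm-by-visit interaction and unstructured covariance. Read the arm difference at a named primary visit, 2 weeks, as section 4.4 uses for sizing. Patients with a baseline angle and at least one post-operative angle then contribute; those with no post-operative angle still do not.

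3. The model assumes data missing at random, so prespecify one sensitivity analysis for data not missing at random.

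No new visits are needed. The model can be fitted in the software named in the addendum, and the addendum is to be registered before it is applied to the closed database, so the rule can be set there. The cost is a slightly less favourable stated power, a little more analysis work and, if loss is expected, possibly more patients within the cap.
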